**7.0 OUTCOME MEASURES**

- Diagnostic accuracy (sensitivity, specificity, positive predictive value, and negative predictive value) of mid-end versus high-end ultrasound machines in detecting ileocolonic involvement in IBD.
- Proportion of patients where clinical management was altered based on IUS findings.

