**SITE OF STUDY**

Asian Institute of Gastroenterology, Somajiguda, Hyderabad

1. **INTRODUCTION**

Inflammatory bowel disease (IBD), comprising Crohn’s disease (CD) and ulcerative colitis (UC), is a chronic, relapsing condition that requires accurate and timely diagnosis for effective management. The gold standard for assessing disease activity includes ileo-colonoscopy and cross-sectional imaging, both of which are costly and often inaccessible in resource-limited settings. Point-of-care ultrasound (POCUS) has emerged as a valuable, cost-effective alternative for managing IBD, particularly in low-resource environments.

Our previous research using a mid-end ultrasound machine (Siemens ACUSON S2000) demonstrated that POCUS significantly influenced clinical management, helping to avoid colonoscopy in more than half of the cases.[1] The study found that POCUS, when compared to ileo-colonoscopy, had a sensitivity of 80% and a specificity of 94.4% for CD, and a sensitivity of 80.8% and a specificity of 92.8% for UC. These results highlight the potential of POCUS to serve as an essential diagnostic tool in the management of IBD, particularly in settings where access to advanced diagnostic modalities is limited.[1]

While mid-end ultrasound machines have shown promise in managing IBD, there is a lack of comparative studies evaluating their diagnostic accuracy against high-end machines. High-end ultrasound devices, offer advanced imaging features such as extended field of view, speckle reduction, and enhanced computing power, which could potentially improve diagnostic accuracy. However, their high cost poses a significant barrier to widespread use, especially in resource-limited settings.

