**Secondary Objectives:**

To evaluate changes in clinical management decisions following IUS with a high-end ultrasound machine compared to a mid-end machine.

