**5.0 DESIGN AND DURATION OF THE STUDY**

Cross-sectional study, follow up until ileo-colonoscopy (same or next day)

Duration of study (Recruitment period) : 6-12 months (estimated sample size 100)

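### The management outcome counts right and wrong changes alike, so it cannot show which machine leads to better decisions

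*Protocol*

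**What the plan says.** Section 7.0 lists two outcomes. The first is "Diagnostic accuracy (sensitivity, specificity, positive predictive value, and negative predictive value) of mid-end versus high-end ultrasound machines". The second, given in full, is the "Proportion of patients where clinical management was altered based on IUS findings". The second carries no condition on the direction of the change, on its correctness, or on agreement with the reference standard, and it names no machine.

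The secondary objective makes it a comparison: "To evaluate changes in clinical management decisions following IUS with a high-end ultrasound machine compared to a mid-end machine".

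The Introduction presents management impact as a merit of ultrasound. It reports that earlier work with the mid-end machine "demonstrated that POCUS significantly influenced clinical management, helping to avoid colonoscopy in more than half of the cases". For accuracy in that work it gives two pairs of figures: for Crohn's disease ultrasound "had a sensitivity of 80% and a specificity of 94.4% for CD", and for ulcerative colitis it had "a sensitivity of 80.8% and a specificity of 92.8% for UC".

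Section 6.0 sorts patients before the scan into flare or relapse, response to new therapy, and clinically quiescent disease. Every patient is scanned on both machines by the same joint team. Ileo-colonoscopy follows on the same or next day, but only where it is clinically indicated. Section 6.0 describes a clinical assessment and documented scan findings; it does not describe a recorded management plan before or after either scan.

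**The concern.** A comparison of two diagnostic devices on management impact is useful only if a higher or lower figure has a meaning. Here it has none. A plan altered because of a false-positive scan, or a colonoscopy dropped after a false-negative one, adds to the numerator exactly as a correct change does. Two machines could show the same proportion with very different shares of wrong changes, or the less accurate one could show the larger proportion.

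The study's rationale is resource allocation between a cheaper and a dearer machine, so readers will want to use this figure. As defined, it does not tell them which machine leads to better decisions, even if every change were credited to the right machine.

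**Working it through.** The protocol states no expected value for this outcome, so there is no figure to reproduce. The check is whether the raw proportion must rise with accuracy.

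**Inputs.** From the Introduction: sensitivity 80% and specificity 94.4% (Crohn's disease); 80.8% and 92.8% (ulcerative colitis). Assumed, because the protocol gives none: the prevalence of active disease, the share of quiescent patients, and the rule that links a scan result to a change.

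**Formula.** P(scan positive) = sens × prev + (1 − spec) × (1 − prev).

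**Step 1: one result drives all changes.** Take the Crohn's disease figures, prevalence 50%, and a comparator with the same sensitivity but specificity 80%.
- Change if positive: 0.80 × 0.5 + 0.056 × 0.5 = 42.8%, against 0.80 × 0.5 + 0.20 × 0.5 = 50.0%. The worse machine scores 7.2 points higher. At prevalence 40% and 60% the gap is 8.6 points (35.4% and 44.0%) and 5.8 points (50.2% and 56.0%).
- Change if negative: 100 − 42.8 = 57.2%, against 100 − 50.0 = 50.0%. The worse machine now scores 7.2 points lower.

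So the sign depends on which result triggers the change.

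**Step 2: the scan contradicts the clinical group.** Assume quiescent patients change if the scan is positive and flare patients change if it is negative, with prevalence 30% and 70%. The response-to-therapy group is left out for simplicity. With the ulcerative colitis figures:
- Quiescent: 0.808 × 0.3 + 0.072 × 0.7 = 0.2424 + 0.0504 = 29.3%.
- Flare: 1 − (0.808 × 0.7 + 0.072 × 0.3) = 1 − 0.5872 = 41.3%.
- Half and half: (0.2928 + 0.4128) / 2 = 35.3%.

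Correct changes are the true positives in quiescent patients and the true negatives in flare patients: (0.2424 + 0.928 × 0.3) / 2 = 26.0%. Wrong changes are the rest: (0.0504 + 0.192 × 0.7) / 2 = 9.2%. The same steps for the other cases, half the patients quiescent, give:

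| Scan | Raw proportion | Correct | Wrong |
|---|---|---|---|
| Perfect | 30.0% | 30.0% | 0% |
| 80.8% / 92.8% | 35.3% | 26.0% | 9.2% |
| Specificity 10 points lower | 37.3% | 24.5% | 12.7% |
| Sensitivity 10 points lower | 37.3% | 24.5% | 12.7% |

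Components may differ from the total by 0.1 through rounding. The raw proportion rises as accuracy falls; the split puts the machines back in order.

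**Step 3: vary the patient mix.** With quiescent share w, lowering specificity by 10 points changes the score by 0.1 × [0.7w − 0.3(1 − w)] = 0.1 × (w − 0.3).
- All quiescent: 29.3% to 36.3%.
- 30% quiescent: 37.7% in both cases.
- All flare: 41.3% to 38.3%.

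Lowering sensitivity by 10 points changes it by 0.1 × (0.7 − w): 29.3% to 26.3% if all are quiescent, and 41.3% to 48.3% if all are in flare.

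**The case against.** The strongest reply is that the protocol already measures accuracy, as its primary comparison and in the same paired patients. A machine with poor specificity would be seen to have it, at least among those who have colonoscopy. That is a real mitigation. It does not close the gap, because nothing ties a given patient's management change to that patient's reference result. Readers would have two separate summaries and no count of wrong decisions.

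A second reply is that an unseen analysis plan could classify the changes. It could, but only if the intended plan was captured before and after each scan, and the protocol describes no such record. A plan not recorded at the time is hard to reconstruct reliably.

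Third, this is a secondary outcome in a study that calls itself a pilot. That limits the weight of the point but does not change what the outcome measures.

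Three stronger readings are tempting and are not supported:
- A reader might infer that more false positives always raise the score. Steps 1 and 3 show that they can also leave it unchanged or lower it. The Introduction's own example of impact, avoided colonoscopy, is plausibly driven by negative scans.
- A reader might infer that the study will present the higher proportion as the better machine. The protocol nowhere says so; the secondary objective only evaluates changes, and the Introduction's praise is for ultrasound in general.
- A reader might infer from the same-day or next-day timing that every change could be verified. Section 6.0 makes colonoscopy conditional on clinical indication, and an avoided colonoscopy leaves no reference result by definition.

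**Conclusion.** The point holds in this form: the outcome in section 7.0 gives correct and incorrect changes equal credit, so the comparison in the secondary objective cannot show which machine leads to better decisions. A machine with more errors, false positive or false negative depending on patient mix and on which result drives the change, can score higher.

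In the worked case the raw proportion runs 30.0%, 35.3%, 37.3% as accuracy declines, in reverse order of merit, while wrong changes run 0%, 9.2%, 12.7%. The step from 35.3% to 37.3% is only two patients per 100, so the lesson is about meaning and not about a large bias. The size and sign rest on the assumed rule, prevalences and mix. That the raw proportion ignores correctness rests on none of them. The amendment is worth making before recruitment, since it depends on data that must be collected prospectively.

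**What to change.** Amend sections 6.0 and 7.0 as follows.
- Record the intended management before any scan, and again for each machine's findings separately, in every case before the colonoscopy result is known. A single plan recorded after both scans would not do, because both machines are used in every patient and the change could not be assigned to either.
- For each machine, report the raw proportion altered, keeping avoided colonoscopies in it, split into changes that agree with ileo-colonoscopy, changes that disagree, and changes unverified because no colonoscopy was done.
- Define agreement in advance as the change matching the colonoscopic activity finding.
- State that a higher raw proportion is not to be read as better performance.

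The cost is a few case report form fields and a short amendment, with no added patients or procedures. The agreement split covers only patients who have colonoscopy, so avoided colonoscopies will fall in the unverified class, and the size of that class should be shown. As the same team scans on both machines, the plan recorded for the second machine will also not be formed in ignorance of the first; that limit should be stated.

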**6.0 METHODOLOGY**

The HUMID (High-end vs. Mid-end Ultrasound in IBD Diagnostics) study is a prospective, paired, validating confirmatory study aimed at comparing the diagnostic accuracy of mid-end versus high-end intestinal ultrasound (IUS) machines in patients with inflammatory bowel disease (IBD) involving the ileocolonic region. The study specifically contrasts the performance of the mid-end Siemens ACUSON S2000 and the high-end Samsung RS85 ultrasound machines, using ileo-colonoscopy as the reference standard.

Upon enrollment, each patient will undergo a clinical assessment by an IBD specialist using the Harvey–Bradshaw Index (HBI) for Crohn’s Disease (CD) and the Simple Clinical Colitis Activity Index (SCCAI) for Ulcerative Colitis (UC). Patients will be categorized into three groups: flare/relapse, response to new therapy, and clinically quiescent disease. Point-of-care ultrasound (POCUS) will be performed using both the Siemens ACUSON S2000 (mid-end) and Samsung RS85 (high-end) machines, with patients asked to fast prior to the examination, though this is not mandatory. The Siemens ACUSON S2000 will utilize a high-frequency linear probe (9 L4, 4–9 MHz) and will use pediatric abdomen and thyroid presets with a trapezoid view for bowel visualization. The Samsung RS85 will employ linear 2-10 MHz and 2-18 MHz probes, offering advanced imaging features such as extended field of view and speckle reduction. Both ultrasound examinations will be conducted jointly by a GI sonologist and an IBD specialist, with findings documented by a research associate and consensus reached by the examiners. Ileo-colonoscopy will be performed on the same or following day if clinically indicated, providing the diagnostic gold standard against which the accuracy of both ultrasound machines will be assessed.

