**9.0** **STATISTICAL ANALYSIS**

Data shall be analyzed to compare the sensitivity, specificity, positive predictive value (PPV), and negative predictive value (NPV) of the mid-end versus high-end ultrasound machines. Paired comparisons between the two machines and against the reference standard (ileo-colonoscopy) shall be conducted using appropriate statistical tests. Statistical Package for the Social Sciences version 26 (Armonk, NY: IBM Corp.) shall be used for statistical analysis and p value <0.05 shall be considered significant.

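### The secondary objective compares management changes between the two machines, but the outcome is one proportion that names no machine, and no decision per machine is described

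*Protocol*

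**What the plan says.** The protocol, under Secondary Objectives, lists a single aim: "To evaluate changes in clinical management decisions following IUS with a high-end ultrasound machine compared to a mid-end machine". This is a contrast between machines.

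Section 7.0 (Outcome Measures) gives the matching outcome as "Proportion of patients where clinical management was altered based on IUS findings". The accuracy outcome directly above it is stated "of mid-end versus high-end ultrasound machines in detecting ileocolonic involvement in IBD", so the section separates the machines for accuracy but not for management.

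Section 6.0 (Methodology) makes the design paired: "Point-of-care ultrasound (POCUS) will be performed using both the Siemens ACUSON S2000 (mid-end) and Samsung RS85 (high-end) machines". The same team handles both scans and agrees the reading: "Both ultrasound examinations will be conducted jointly by a GI sonologist and an IBD specialist". It gives no scan order, no arrangement to keep one machine's findings from whoever judges the other's, and no management decision recorded for each machine. Section 5.0 ends follow-up at ileo-colonoscopy, on the same or next day. Section 8.0 plans 100 patients.

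**The concern.** A patient scanned on both machines has one actual course of management. If it is settled once both sets of findings are known, it cannot afterwards be divided between the machines. An outcome that counts patients whose management changed because of ultrasound then describes the two scans together, whereas the objective asks how they differ.

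The rationale in section 2.0 is whether the cheaper machine can match the dearer one. A proportion resting on both scans could be read as what the mid-end machine achieves alone, and the planned data would neither confirm nor refute that reading. The gap lies in what is collected, so it has to be closed before recruitment.

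**Working it through.** **Inputs.** N = 100 (section 8.0). The documents give no expected rate of management change, so a pooled proportion of 50% is assumed, with 30% and 60% as a range. Section 8.0 gives no effect size, power or rate, so there is no figure of the plan's own to reproduce. The check is whether the outcome identifies the quantity that the objective asks for.

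**Notation.** Of the 100 patients, a would have management altered on either machine's findings taken alone, b on the high-end findings only, c on the mid-end findings only, and d on neither.

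- The objective needs: difference = (b - c)/N.
- The outcome, read as altered on either scan, gives: P = (a + b + c)/N.

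**Step 1: what P says about the difference.** P = 0.50 means a + b + c = 50.

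- All high-end only (b = 50, a = c = 0): difference = +50 points.
- All mid-end only (c = 50, a = b = 0): difference = -50 points.
- Every value in between is possible, so in general the difference lies anywhere from -P to +P: -30 to +30 points at P = 30%, and -60 to +60 at P = 60%.

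**Step 2: three splits with the same reported result.**

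| a | b | c | Reported P | Difference | Exact McNemar p |
|---|---|---|---|---|---|
| 40 | 5 | 5 | 50% | 0 points | 1.00 |
| 40 | 10 | 0 | 50% | +10 points | 0.002 |
| 40 | 0 | 10 | 50% | -10 points | 0.002 |

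For 10 against 0, p = 2 × 0.5^10 = 0.00195. The outcome as written cannot tell equal machines from a clear advantage in either direction.

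**Step 3: precision does not help.** The 95% half-width for P is 1.96 × sqrt(0.50 × 0.50/100) = 0.098, or 9.8 points (9.0 at 30%, 9.6 at 60%). The pooled proportion is estimated tolerably well, but it is a different quantity from the one in the objective.

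**Step 4: dependence on the reading.** Suppose management were altered only when both scans pointed that way. Then P = a/N and b + c can be anything up to N - a, so the difference lies within plus or minus (1 - P): 50 points at P = 50%, 70 at 30%, 40 at 60%. The rule changes the limits, but the difference remains unidentified.

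**The case against.** The strongest reply is that the outcome in section 7.0 is shorthand. The objective states the comparison, the accuracy outcome requires findings kept separately by machine, and section 9.0 promises "Paired comparisons between the two machines and against the reference standard (ileo-colonoscopy) shall be conducted using appropriate statistical tests". On this view the management proportion would simply be tabulated by machine, with details left to the analysis plan. It is also a secondary outcome in a study that section 8.0 calls a pilot.

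Part of this stands. Separate findings by machine should exist, and a per-machine decision could be built on them. The choice of test belongs to the analysis plan, so section 9.0's silence on this outcome is no fault. But separate findings are not separate decisions. A proportion can be tabulated by machine only if someone records, for each machine, what would be done on its findings, and no such step is described.

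A reader might also infer stronger claims that the documents do not support:

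- *That scanning everyone on both machines defeats the objective.* It does not. A paired design can answer the question if decisions are recorded per machine.
- *That the protocol rules out a decision between scans.* It is silent on this.
- *That the pooled figure overstates one machine's effect.* That assumes either scan alone triggers a change. If each machine alone would alter 50% of patients, with 40% shared, an either-scan rule gives 50 + 50 - 40 = 60%, but a both-must-agree rule gives 40%. The direction is open.
- *That the first machine used will take most of the credit.* The protocol nowhere proposes to credit changes in scan order.

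**Conclusion.** The objective and its outcome do not match. As written, the only secondary objective gets a single proportion that does not identify the difference between machines: at an assumed pooled 50% of 100 patients, read as altered on either scan, anything from -50 to +50 points fits. The 50% and the either-scan reading are assumptions. The failure to identify the difference does not depend on them.

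The conclusion goes no further than that. It asserts no bias in a given direction, leaves the primary accuracy comparison untouched, and does not make the objective unanswerable in this design. It should be corrected before recruitment, because later analysis cannot supply decisions that were not recorded.

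**What to change.** Reconcile the Secondary Objectives with section 7.0 by defining the outcome per machine: the proportion of patients whose intended management changes from the pre-scan plan on the high-end findings alone, and the same proportion on the mid-end findings alone.

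In section 6.0, add a record of the plan before scanning and a separate intended decision from each machine's findings. Randomise the order of scans or reports, and lock the first decision before the second set of findings is seen. Where an IBD specialist already on the team did not scan the patient and is available, that specialist can decide from reports with the machine masked. The protocol does not say how many such specialists there are, so the sponsor should confirm this.

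Compare the two decisions within patient: paired 2x2 table, McNemar test, and difference with 95% CI. Report the proportion whose actual management changed after both scans descriptively.

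Cost: one extra case report form page per patient, two decisions each (200 for 100 patients), and no extra patients or scans. There are two limits. The per-machine decision is intended rather than carried out. Carry-over between scans by the same examiners is reduced but not removed, because masking a report does not undo what the examiners saw on the other machine.

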**8.0 SAMPLE SIZE CALCULATION**

This is a pilot study and hence we plan to recruit 100 patients to have a reasonable sample size for achieving clinical significance

**9.0** **STATISTICAL ANALYSIS**

Data shall be analyzed to compare the sensitivity, specificity, positive predictive value (PPV), and negative predictive value (NPV) of the mid-end versus high-end ultrasound machines. Paired comparisons between the two machines and against the reference standard (ileo-colonoscopy) shall be conducted using appropriate statistical tests. Statistical Package for the Social Sciences version 26 (Armonk, NY: IBM Corp.) shall be used for statistical analysis and p value <0.05 shall be considered significant.

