**2.0 RATIONALE**

The HUMID study addresses the critical need to evaluate the diagnostic accuracy of mid-end versus high-end intestinal ultrasound (IUS) machines in the context of inflammatory bowel disease (IBD) with ileocolonic involvement. In resource-limited settings, access to advanced diagnostic tools such as colonoscopy and cross-sectional imaging is often scarce, making point-of-care ultrasound (POCUS) an essential, cost-effective alternative for managing IBD.[2] While high-end ultrasound machines offer superior imaging quality through advanced features such as extended field of view, speckle reduction, and enhanced computing power, their high procurement costs limit their accessibility. Mid-end machines, equipped with high-frequency probes (≥5 MHz), provide a more affordable option, potentially enabling broader dissemination of POCUS in settings where resources are constrained. However, there is a perceived gap in the diagnostic precision of mid-end machines, as current literature on their efficacy remains limited. This study seeks to validate whether mid-end ultrasound machines can reliably match the diagnostic accuracy of high-end machines when compared to the gold standard of ileo-colonoscopy, ultimately aiming to inform resource allocation and optimize IBD management in diverse healthcare environments.

1. **STUDY OBJECTIVES**

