**3a. Primary objective**

To compare the diagnostic accuracy of intestinal ultrasound (IUS) using a high-end ultrasound machine versus a mid-end ultrasound machine in relation to ileo-colonoscopy for assessing ileocolonic involvement in IBD.

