   - **Confidentiality:** Patient confidentiality will be rigorously protected. All data collected will be anonymized and securely stored, ensuring privacy and ethical handling of patient information.
4. **Clinical Relevance and Utility:**
   - **Direct Clinical Impact:** The study’s outcomes will have immediate clinical applications. If the mid-end ultrasound proves to be as effective as the high-end model, it could facilitate broader adoption of ultrasound technology in settings with limited resources, thus improving patient care and diagnostic efficiency.
5. **Multidisciplinary Approach:**
   - **Comprehensive Evaluation:** The study involves a multidisciplinary team of gastroenterologists, ultrasound specialists, and researchers, ensuring a thorough and objective evaluation of the imaging techniques.

In summary, the HUMID study is ethically justified as it seeks to enhance patient care by validating a cost-effective diagnostic tool, potentially reducing the reliance on invasive procedures, and improving the management of inflammatory bowel disease. The study’s design incorporates thorough informed consent, minimizes risk, and maintains confidentiality, further supporting its ethical integrity.

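### The plan aims to show that the mid-end machine matches the high-end one, but its only criterion is p<0.05, with no margin or confidence-interval rule

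*Protocol*

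**What the plan says.** - **Aim.** Protocol section 2.0 (Rationale): "This study seeks to validate whether mid-end ultrasound machines can reliably match the diagnostic accuracy of high-end machines". The study title and section 6.0 both describe the study as validating and confirmatory.
- **Intended use.** Section 10.0, item 4, foresees broader adoption under this condition: "If the mid-end ultrasound proves to be as effective as the high-end model".
- **Formal objective.** Section 3a is neutral: "To compare the diagnostic accuracy of intestinal ultrasound (IUS) using a high-end ultrasound machine versus a mid-end ultrasound machine".
- **Analysis.** In section 9.0, paired comparisons of the machines with each other and with ileo-colonoscopy "shall be conducted using appropriate statistical tests". The one criterion is "p value <0.05 shall be considered significant".
- **Size.** Section 8.0 calls the study a pilot and states "we plan to recruit 100 patients to have a reasonable sample size for achieving clinical significance". It gives no effect size, power, discordance or margin.
- **Verification.** Under section 6.0, ileo-colonoscopy is done only where clinically indicated, so the number with a reference standard may be below 100.

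**The concern.** Saying that a cheaper machine matches a dearer one is a non-inferiority or equivalence claim. It needs a statement of how much accuracy may be lost, and a rule that the data must exclude a larger loss. The protocol has neither. A criterion of p<0.05 applied to a comparison can establish that the machines differ. Failing to meet it establishes nothing, because p≥0.05 becomes more likely as the sample shrinks, whatever the truth.

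At stake is the use the protocol itself foresees, adoption of the mid-end machine where resources are limited. If it misses active disease that the high-end machine finds, a study of this size could easily fail to show it, and section 9.0 contains nothing to stop that result being cited in support of the stated aim.

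**Working it through.** **The plan's own figure.** N=100 cannot be reproduced, because section 8.0 gives no inputs. The figures below are illustrations, for sensitivity only.

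**Inputs**
- Mid-end sensitivity 80%: section 1 reports 80% for Crohn's disease and 80.8% for ulcerative colitis.
- High-end sensitivity 90%: assumed.
- Discordant pairs among the diseased, 15%: assumed.
- Diseased patients with ileo-colonoscopy, n = 30, 60 or 100: assumed. The last is an extreme case, since it leaves nobody for specificity.
- Two-sided α = 0.05: section 9.0 gives 0.05; two-sided is assumed.

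**Step 1: discordant cells.** Let p10 be the share positive on high-end only and p01 the share positive on mid-end only. Then p10 − p01 = 0.10 and p10 + p01 = 0.15, so p10 = 0.125 and p01 = 0.025.

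**Step 2: chance that the real 10-point deficit gives p≥0.05.** The number of discordant pairs m is Binomial(n, 0.15). Given m, the number favouring high-end is Binomial(m, 0.125/0.15), tested against Binomial(m, 0.5). Summing over all outcomes gives:

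| Diseased and verified | Exact McNemar | Mid-p McNemar |
|---|---|---|
| 30 | 90.7% | 81.6% |
| 60 | 60.0% | 48.8% |
| 100 | 30.5% | 23.0% |

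The result depends on the assumed discordance. With 100 diseased and the exact test, it runs from 5.8% (10% discordant) to 45.6% (20% discordant).

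**Step 3: what a margin rule would do instead.** Rule: the lower limit of the paired 95% interval (Agresti–Min) for mid minus high must lie above minus the margin. Discordance is 15% throughout. The acceptance columns use the cells of step 1; the equal-machines columns use p10 = p01 = 0.075.

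| Diseased and verified | Equal machines, 10-point margin: shown | Equal machines, 15-point margin: shown | 10 points worse, 10-point margin: accepted | 10 points worse, 15-point margin: accepted |
|---|---|---|---|---|
| 30 | 32% | about 55% | about 4% | 13% |
| 60 | 52% | about 85% | about 4% | 23% |
| 100 | 74% | 97% | about 4% | 30% |

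**Step 4: size needed for a margin rule.** For truly equal machines, n = pd × (z0.975 + z0.80)² / margin², where pd is the discordant share. With pd = 0.15 and a 10-point margin, n = 0.15 × (1.960 + 0.842)² / 0.01 ≈ 118 diseased and verified patients, more than the whole planned recruitment. With pd = 0.10 it is 79, and with pd = 0.20 it is 157. Specificity needs its own count of patients negative on the reference standard.

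**The case against.** The strongest defence is that the protocol promises less than this point supposes. The primary objective, the outcome measures and section 9.0 speak only of comparing. The matching language stands in the rationale and in a conditional sentence of the ethics section, and section 8.0 calls the study a pilot. Unnamed appropriate tests could include a non-inferiority test, and the test and interval method may properly be left to a statistical analysis plan.

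Part of this stands, and it rules out three stronger readings that a reader might infer:
- **That the protocol commits itself to a two-sided test of difference.** It names no test and no sidedness.
- **That it will read p≥0.05 as equivalence.** No sentence says so. That step is an inference from the stated aim and the single criterion.
- **That an inferior machine would usually pass.** Under the assumptions above, that holds with 30 diseased patients. It is close to an even chance with 60, and does not hold with 100.

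What does not stand is the defence that nothing is missing. A non-inferiority test cannot be run without a margin. The margin and the type of hypothesis determine what the study may conclude and how large it must be, so they are not details of test choice. The protocol already fixes the aim, N and the significance criterion, and these do not fit together. The pilot label is offset by the confirmatory label in the title and section 6.0.

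**Conclusion.** The point holds in this form: as written, the plan has no result that could support its conclusion of matching accuracy. A significant p-value could show a difference, but a non-significant one is not evidence of its absence. A real 10-point loss of sensitivity would go undetected in roughly a quarter to nine-tenths of studies, depending mainly on how many patients are diseased and verified. Those sizes rest on the assumed 90% high-end sensitivity, 15% discordance and 30–100 diseased patients; only the 80% mid-end sensitivity and the 0.05 level come from the document. The mismatch between aim and criterion does not depend on those assumptions.

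**What to change.** In section 9.0:
1. Make the primary result the paired difference (mid minus high) in sensitivity and in specificity, each with a paired 95% confidence interval.
2. State that p≥0.05 is not evidence of equivalence.
3. Fix and clinically justify a margin before any data are seen. Allow a conclusion that the mid-end machine matches, or is as effective, only if the lower confidence limit lies above minus that margin. Otherwise report the result as inconclusive.
4. If no margin can be justified at N=100, limit the aim to estimation with confidence intervals and remove the matching and equal-effectiveness conclusions from sections 2.0 and 10.0.

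**Cost.** The change is to wording, but the claim becomes harder to earn. With truly equal machines, 15% discordance and a 10-point margin, non-inferiority would be shown in only about 32%, 52% or 74% of studies with 30, 60 or 100 diseased patients. Widening the margin to 15 points raises these to about 55%, 85% and 97%, but would then accept a machine 10 points worse in about 13–30% of studies. If the claim is to be kept with a 10-point margin, the sample size must be revisited as well, counting reference-positive and reference-negative patients separately. The estimation option in item 4 needs no more patients.
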